## Abstract

**Background:**

Acute appendicitis is one of the most common indications for emergency surgery. In patients with a complex appendicitis, prolonged antibiotic prophylaxis is recommended after appendectomy. There is no consensus regarding the optimum duration of antibiotics. Guidelines propose 3 to 7 days of treatment, but shorter courses may be as effective in the prevention of infectious complications. At the same time, the global issue of increasing antimicrobial resistance urges for optimization of antibiotic strategies. The aim of this study is to determine whether a short course (48 h) of postoperative antibiotics is non-inferior to current standard practice of 5 days.

**Methods:**

Patients of 8 years and older undergoing appendectomy for acute complex appendicitis – defined as a gangrenous and/or perforated appendicitis or appendicitis in presence of an abscess – are eligible for inclusion. Immunocompromised or pregnant patients are excluded, as well as patients with a contraindication to the study antibiotics. In total, 1066 patients will be randomly allocated in a 1:1 ratio to the experimental treatment arm (48 h of postoperative intravenously administered (IV) antibiotics) or the control arm (5 days of postoperative IV antibiotics). After discharge from the hospital, patients participate in a productivity-cost-questionnaire at 4 weeks and a standardized telephone follow-up at 90 days after appendectomy. The primary outcome is a composite endpoint of infectious complications, including intra-abdominal abscess (IAA) and surgical site infection (SSI), and mortality within 90 days after appendectomy. Secondary outcomes include IAA, SSI, restart of antibiotics, length of hospital stay (LOS), reoperation, percutaneous drainage, readmission rate, and cost-effectiveness. The non-inferiority margin for the difference in the primary endpoint rate is set at 7.5% (one-sided test at ɑ 0.025). Both per-protocol and intention-to-treat analyses will be performed.

**Discussion:**

This trial will provide evidence on whether 48 h of postoperative antibiotics is non-inferior to a standard course of 5 days of antibiotics. If non-inferiority is established, longer intravenous administration following appendectomy for complex appendicitis can be abandoned, and guidelines need to be adjusted accordingly.

**Trial registration:**

Dutch Trial Register, NTR6128. Registered on 20 December 2016.

**Electronic supplementary material:**

The online version of this article (10.1186/s13063-018-2629-0) contains supplementary material, which is available to authorized users.

## Background

Acute appendicitis is one of the most common surgical emergencies in children and adults worldwide [1–3]. Although the role of surgery as primary treatment has recently been questioned, appendectomy remains the treatment of choice [4, 5]. In the Netherlands, more than 12,000 patients undergo appendectomy for acute appendicitis each year [6]. In Northern America the estimated number of patients with appendicitis in 2015 was over 378,000 [7]. Intraoperatively, acute appendicitis is classified as either simple or complex. A phlegmonous appendix is considered simple. A complex appendicitis includes a gangrenous and/or perforated appendix as well as any appendicitis with an intra-abdominal or pelvic abscess (IAA) [8]. Previously, it was thought that a simple appendicitis could progress towards a complex appendicitis over time, but more recent data suggest that both entities represent distinct types of inflammation [8, 9]. Some 25–30% of all patients with appendicitis have a complex appendicitis, which is associated with increased risk of postoperative infectious complications [10–14]. Therefore, following perioperative antibiotic prophylaxis, guidelines recommend postoperative antibiotics for complex appendicitis [15–18].

Currently, there is no consensus on the duration of postoperative antibiotic treatment and different antibiotic regimens are used [8, 19–21]. A nationwide cohort study from the Netherlands showed that most patients receive 5 days of postoperative antimicrobial therapy [22]. However, it may be safe to stop intravenously administered (IV) antibiotic treatment earlier than 5 days, when a patient meets defined discharge criteria (patient is afebrile, has a normal leukocyte count, has resumed oral intake) [10, 14, 23–29]. Cohort studies show that 3 days of postoperative antibiotic treatment is feasible and safe [12, 30–32]. At least 48 h of IV antibiotics is recommended in the Dutch surgical guideline [15]. Small retrospective studies show that even postoperative prophylaxis of less than 3 days is feasible [33–36]. However, the methodological quality of these studies is poor. Therefore, no definite recommendations can be made regarding the optimum duration of postoperative prophylaxis after appendectomy for complex appendicitis. To date, no randomized clinical trial has been published to address this topic in an adequately powered study population.

Furthermore, there is a growing global health issue of bacterial resistance. Antimicrobial resistance is a natural biological outcome of antibiotic use and antibiotic overtreatment speeds up this process [37]. Hence, restricting antibiotic therapy is warranted, as pointed out in a report by the World Health Organization [38]. This study aims to evaluate efficacy of a restrictive postoperative antibiotic course as compared to standard regimen for complex appendicitis, in a non-inferiority design. This manuscript is prepared in accordance with the Standard Protocol Items: Recommendations for Interventional Trials (SPIRIT) guidelines [39].

### Trial objective and hypothesis

The primary objective of this study is to evaluate the efficacy and safety of discontinuing antibiotic treatment after 48 h, compared to completing a standard course of 5 days after appendectomy for complex acute appendicitis. It is hypothesized that a 48-h course is non-inferior to 5 days and will not result in an increase of infectious complications and mortality. Secondary aims are to evaluate length of hospital stay and cost-effectiveness.

## Methods

### Trial design

The *A*ntibiotics following a*PP*endectomy *I*n *C*omplex appendicitis (APPIC) trial is a phase IV, prospective, multicenter, non-blinded, randomized controlled trial powered for non-inferiority. Patients are randomly allocated to a short course of 48 h (intervention arm), or the standard course of 5 days (control arm) of IV antibiotics following appendectomy for complex appendicitis. An overview of enrollment, interventions, and follow-up of participants in the APPIC trial is shown in Fig. 1. Figure 2 shows the Standard Protocol Items Recommendations for Interventional Trials (SPIRIT) Figure. The SPIRIT Checklist is shown in Additional file 1.

**Fig. 1 Fig1:**
[figure not shown]
APPIC flowchart of inclusion and randomization. Legend: * All except intraoperative criteria regarding type of appendicitis; ** If the patient has not been able to give informed consent prior to appendectomy, this may still be acquired postoperatively, as long as inclusion and randomization takes place within 24 h; *** Intravenously administered antibiotic treatment continues for three more days to complete 5 days in total

**Fig. 2 Fig2:**
[figure not shown]
APPIC schedule of enrollment, interventions, and assessments

### Trial setting

The trial will run in at least 14 hospitals in the Netherlands. This includes one academic hospital and 13 teaching hospitals. The participating hospitals are listed on the trial webpage (www.appictrial.nl). In all participating hospitals appendectomy is mostly performed laparoscopically.

### Eligibility criteria

Patients of at least 8 years of age who are scheduled to undergo surgery for suspected acute appendicitis will be approached for participation in the study. If a complex appendicitis is diagnosed intraoperatively, patients are eligible for inclusion. A complex appendicitis is defined as a gangrenous and/or perforated appendicitis or any appendicitis in presence of an IAA [8]. Written informed consent is preferably obtained before surgery, but may be obtained postoperatively as long as inclusion and randomization is performed within 24 h after surgery. Exclusion criteria are:Unable to give informed consent (language barrier, legally incapable)Interval appendectomyClinical suspicion of severe sepsis*Conservative treatment of acute appendicitisAmerican Society of Anesthesiologists (ASA) score IV or not able to undergo surgeryKnown allergy or other contraindication to study medication*Immunocompromised patients*PregnancyConcurrent use of antibiotics for other indication*Simple acute appendicitis*Appendicular infiltrate not amendable for appendectomyInadequate source control in opinion of the surgeon*

* more elaborate definitions are given in the full study protocol.

### Interventions

#### Postoperative antibiotic treatment

Participants will be randomized (1:1) to receive either: (1) a short course of 48 h or (2) a standard 5-day course of postoperative antibiotic treatment. All patients receive IV antibiotics during the first 48 h after appendectomy: cefuroxime/metronidazole (three times a day, 1500/500 mg), or alternatively ceftriaxone/metronidazole (once a day, 2000 mg/three times a day, 500 mg) according to local antibiotic policy. In the control group the IV antibiotics are continued for three more days (a switch to an oral formula is not allowed). A daily dose of gentamicin as co-intervention is optional. No other antibiotics are permitted.

#### Criteria for modifying the allocated treatment

Antibiotic treatment may be prolonged or restarted only in case of a proven source of infection (a decision algorithm is provided in the full protocol). A switch to a different antibiotic regimen is allowed only if necessary due to an adverse reaction to the antibiotics or if indicated by culture results (if a micro-organism resistant to cefuroxime (or ceftriaxone) is cultured a switch should be made to ensure effective antibiotic treatment).

#### Discharge and follow-up

Laboratory tests, imaging studies, and blood cultures will be performed only when clinically indicated. The following clinical parameters will be registered on a daily basis: body temperature < 38° Celsius, able to tolerate oral intake, able to mobilize independently; Visual Analog Scale (VAS) < 4 requiring only orally administered analgesia. However, these criteria are not mandatory for discharge and ultimately the responsible physician decides when a patient is able to go home. After discharge a standard outpatient visit is planned at 2 to 4 weeks according to local hospital policy. Four weeks after appendectomy, patients are asked to complete a productivity-cost questionnaire. At 90 days after appendectomy a standardized follow-up by telephone will be conducted.

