### Outcome measures

All outcome measures will be registered directly from the electronic patient files. Outcome assessors will not be blinded for the treatment allocation. The telephone follow-up is introduced to check missing data on the primary endpoint; e.g., visits to hospitals or medical facilities other than the center where the patient was treated and included into the trial.

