#### Primary outcome measure

The primary endpoint of this trial is a composite endpoint of infectious complications related to appendectomy, including IAA and surgical site infection (SSI), and mortality within 90 days after appendectomy. An IAA is defined as an infection that involves the abdominal part of the body deeper than the fascial/muscle layers that is opened or manipulated during the operative procedure. IAA can be diagnosed through imaging or during reintervention, through purulent drainage from a drain placed into the IAA, or isolation of organisms from a culture of the IAA [40]. An SSI can be either deep or superficial, involving the skin, subcutaneous tissue and/or deep soft tissues of the incision. IAA and SSI are defined in more detail according to the Center for Disease Control (CDC) criteria in the full study protocol [40].

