#### Secondary outcome measures

Secondary endpoints are separate rates of IAA, SSI and mortality; duration of antibiotic treatment; the antibiotic regimen; proportion of patients that restarted antibiotics; length of hospital stay (LOS); time to fulfill discharge criteria; postoperative complications; reoperation; percutaneous drainage; number of visits to the general practitioner (GP), emergency room (ER) and outpatient clinic; readmission rate; adverse events on antibiotics; and cost-effectiveness. Complications will be classified according to the Clavien-Dindo classification of surgical complications as well as the Comprehensive Complication Index (CCI). To analyze cost-effectiveness, the validated Institute for Medical Technological Assessment – Productivity Cost Questionnaire (iMTA-PCQ) (version October 2012) will be used, enhanced with a section concerning school absence.

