#### Secondary endpoints

General patient characteristics and other clinically relevant parameters will be compared between the intervention group and the control group with the independent samples Student’s *t* test or the Mann-Whitney test in case of continuous outcome variables and the chi-square or Fisher’s exact test in case of categorical outcome variables where appropriate. All secondary endpoints will be compared between the trial arms using linear regression for continuous outcomes and logistic regression for dichotomous outcomes, with adjustment for age, sex, surgical approach (open versus laparoscopic), type of appendicitis, ASA score, and center. In case of non-normally distributed continuous outcomes, appropriate transformation of these outcomes will be applied. A two-sided significance level of 0.05 will be used for all secondary analyses. Uncertainty with respect to cost-effectiveness will be analyzed by bootstrapping results for incremental costs and health effects. The results will be shown in an acceptability curve that indicates the probability that the intervention meets several cost-effectiveness thresholds.

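### Work and school absence is measured once, at 4 weeks, while complications are counted to 90 days, so later absence is missing from the cost-effectiveness analysis

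*Protocol article*

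**What the plan says.** All places are in the protocol article.

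- **Productivity loss.** Discharge and follow-up states: "Four weeks after appendectomy, patients are asked to complete a productivity-cost questionnaire". The abstract gives the same schedule: "patients participate in a productivity-cost-questionnaire at 4 weeks and a standardized telephone follow-up at 90 days after appendectomy".
- **Instrument.** Under Secondary outcome measures, the iMTA-PCQ "will be used, enhanced with a section concerning school absence" for the cost-effectiveness endpoint. Data collection and management names the same questionnaire for the cost analysis.
- **Complications.** The primary endpoint is a composite of "infectious complications related to appendectomy, including IAA and surgical site infection (SSI), and mortality within 90 days after appendectomy".
- **Later contact.** "At 90 days after appendectomy a standardized follow-up by telephone will be conducted". Its purpose is given under Outcome measures: "The telephone follow-up is introduced to check missing data on the primary endpoint". No productivity or absence items are mentioned for it.
- **Health-care use.** Secondary outcome measures lists "number of visits to the general practitioner (GP), emergency room (ER) and outpatient clinic; readmission rate", along with reoperation, percutaneous drainage and length of stay. Outcome measures says that outcomes are taken from the electronic patient files.
- **Analysis.** "Uncertainty with respect to cost-effectiveness will be analyzed by bootstrapping results for incremental costs and health effects". The article states no time horizon for this analysis.

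**The concern.** Costs and health effects are to be combined in one incremental analysis, but one cost component is observed for a shorter period than the complications that may cause it. A patient with an abscess in week 6, or one from week 3 who is still off work in week 7, counts as a complication, yet the absence after week 4 has no described point of collection.

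The two sides of the comparison are also observed unequally. The expected gain of the short course, an earlier discharge, falls mostly inside the first 4 weeks. Absence caused by infectious complications can run beyond them. Bootstrapping and an acceptability curve express sampling uncertainty; they cannot restore a period in which nothing was measured.

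Cost-effectiveness is a stated secondary aim (Trial objective and hypothesis), and absence data that are not collected prospectively are hard to recover later.

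**Working it through.** **1. The plan's own figures.** This point does not rest on the sample size, but 480 per arm and the 15% rate are used below, so they were checked first. With 15% in both arms, a 7.5-point margin, one-sided 0.025 and 90% power:

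n per arm = 2 × 0.15 × 0.85 × (1.960 + 1.282)² / 0.075² = 477 (rounded up)

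The article states 480, which gives 90.2% power. Allowing for 10% dropout, 960 / 0.90 = 1067, against a stated 1066. Both figures reproduce.

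**2. The two windows.** Four weeks is 28 days. 28/90 = 31% of the endpoint window lies before the questionnaire and (90 − 28)/90 = 62/90 = 69% after it. This is a share of calendar days, not of productivity loss.

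**3. Size of the omission.** Two inputs are not in the documents and are assumed:

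- f, the share of primary events occurring after day 28: 2% to 20%.
- L, the days of work or school lost per late event: 5 to 20.

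Unrecorded days per patient in an arm = event rate × f × L. Unrecorded difference between arms = rate difference × f × L, with the same f and L in both arms.

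| Quantity | Low (f = 0.02, L = 5) | High (f = 0.20, L = 20) |
|---|---|---|
| Late events per 480 patients at 15% (72 × f) | 1.4 | 14.4 |
| Unrecorded days per patient, one arm at 15% | 0.15 × 0.02 × 5 = 0.015 | 0.15 × 0.20 × 20 = 0.60 |
| Unrecorded difference, arms equal | 0 | 0 |
| Unrecorded difference, arms 7.5 points apart | 0.075 × 0.02 × 5 = 0.0075 | 0.075 × 0.20 × 20 = 0.30 |

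**4. A case in which the trial succeeds.** A 7.5-point difference is the boundary of the margin. Non-inferiority can also be shown with a smaller observed excess. At 480 per arm, with 15% in control and 17.8% in the short arm, the unadjusted standard error is √(0.15 × 0.85/480 + 0.178 × 0.822/480) = 0.0239, and the upper limit is 0.028 + 1.96 × 0.0239 = 0.0748, just under 7.5%. The unrecorded difference is then 0.028 × 0.02 × 5 = 0.003 to 0.028 × 0.20 × 20 = 0.11 days per patient.

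**5. What the calculation leaves out.** It counts only events that begin after day 28. Absence that began earlier and continued past week 4 is also cut off, and would add to these figures by an amount the documents do not let one estimate.

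**The case against.** The best reply is that the article is a condensed protocol. It refers to the full protocol for the list of variables, the schedule figure is not shown, and no horizon is stated, so a further collection point or a deliberate 4-week productivity horizon cannot be excluded. That stands as a caution. It does not remove the point: the article gives a definite time for the questionnaire twice and a different purpose for the later call, so this is a stated schedule and not merely a detail left out.

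The reply is right about several stronger readings that a reader might infer:

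- **That late costs in general are lost.** They are not. Readmission, reoperation, drainage and GP, emergency-room and outpatient visits are outcomes separate from the questionnaire. A late abscess can enter as direct cost; only the absence it causes is missing. The article gives no explicit 90-day window for these items, so the mismatch rests on the primary endpoint alone.
- **That the analysis favours the short course.** This needs more late or prolonged absence in that arm. The documents give no timing of complications and no evidence of an imbalance, and the planning assumption is 15% in both arms.
- **That the effect is large.** The upper figures combine the margin boundary with the high end of unsourced assumptions.
- **That the margin loses its support.** Rationale for the chosen study design ties cost to reduced antibiotic consumption and lower medical care costs, not to productivity savings.

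**Conclusion.** The point holds in a limited form. As described, productivity and school-absence loss after week 4 is not captured, although complications are counted to 90 days. The direction of any bias is conditional: the productivity cost of whichever arm has more complications is understated, and with equal complications the omission largely cancels.

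Its size cannot be derived from the documents. Under the assumed ranges it runs from 0.0075 to 0.30 days per patient at a full 7.5-point difference, excluding absence carried over from before week 4, and it may well be small. One component of one secondary endpoint is affected; the non-inferiority test and the sample size are untouched. This is a cheap improvement, not a flaw in the trial's main inference.

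**What to change.** Add work-absence and school-absence items covering week 4 to day 90 to the standardised 90-day telephone call, which is already planned for all patients. Run the cost-effectiveness analysis on one stated 90-day horizon for both costs and effects. Add a sensitivity analysis with a 4-week productivity horizon that includes patients already past day 90 when the items are introduced. If collection cannot be extended, limit the productivity-cost conclusion to 4 weeks and say so.

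The cost is a form update and a few more minutes per call. There are two downsides. Recall is longer for the second period than for the first. Coverage is also incomplete: 165 of the planned 1066 patients had been randomised when the article was completed (Trial status), so from that point (1066 − 165)/1066 = 901/1066, about 85%, were still to be enrolled and could have been covered prospectively. The share still reachable now depends on how far recruitment has advanced.

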### Outcome measures

All outcome measures will be registered directly from the electronic patient files. Outcome assessors will not be blinded for the treatment allocation. The telephone follow-up is introduced to check missing data on the primary endpoint; e.g., visits to hospitals or medical facilities other than the center where the patient was treated and included into the trial.

#### Primary outcome measure

The primary endpoint of this trial is a composite endpoint of infectious complications related to appendectomy, including IAA and surgical site infection (SSI), and mortality within 90 days after appendectomy. An IAA is defined as an infection that involves the abdominal part of the body deeper than the fascial/muscle layers that is opened or manipulated during the operative procedure. IAA can be diagnosed through imaging or during reintervention, through purulent drainage from a drain placed into the IAA, or isolation of organisms from a culture of the IAA [40]. An SSI can be either deep or superficial, involving the skin, subcutaneous tissue and/or deep soft tissues of the incision. IAA and SSI are defined in more detail according to the Center for Disease Control (CDC) criteria in the full study protocol [40].

#### Secondary outcome measures

Secondary endpoints are separate rates of IAA, SSI and mortality; duration of antibiotic treatment; the antibiotic regimen; proportion of patients that restarted antibiotics; length of hospital stay (LOS); time to fulfill discharge criteria; postoperative complications; reoperation; percutaneous drainage; number of visits to the general practitioner (GP), emergency room (ER) and outpatient clinic; readmission rate; adverse events on antibiotics; and cost-effectiveness. Complications will be classified according to the Clavien-Dindo classification of surgical complications as well as the Comprehensive Complication Index (CCI). To analyze cost-effectiveness, the validated Institute for Medical Technological Assessment – Productivity Cost Questionnaire (iMTA-PCQ) (version October 2012) will be used, enhanced with a section concerning school absence.

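### The restart endpoint is not comparable between arms: an infection proven between 48 h and day 5 can count as a restart only in the short-course arm

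*Protocol article*

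**What the plan says.** Under Postoperative antibiotic treatment, both arms receive IV antibiotics for the first 48 h. The short arm then stops. For the other arm the article says: "In the control group the IV antibiotics are continued for three more days", with no oral switch.

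Under Criteria for modifying the allocated treatment, prolonging and restarting are two actions under one rule: "Antibiotic treatment may be prolonged or restarted only in case of a proven source of infection". A change of regimen is a third action, allowed for an adverse reaction or on culture results. The decision algorithm is left to the full protocol.

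Under Secondary outcome measures, only one of these actions is an endpoint. The list includes "proportion of patients that restarted antibiotics; length of hospital stay (LOS); time to fulfill discharge criteria" and, later, "readmission rate; adverse events on antibiotics; and cost-effectiveness". Duration of antibiotic treatment and the separate abscess and surgical site infection rates are also listed.

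Under Discharge and follow-up, the daily criteria are "body temperature < 38° Celsius, able to tolerate oral intake, able to mobilize independently; Visual Analog Scale (VAS) < 4 requiring only orally administered analgesia", and "these criteria are not mandatory for discharge".

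Under Secondary endpoints in the statistical section, dichotomous outcomes go to logistic regression and continuous outcomes to linear regression. Both are adjusted for baseline covariates and center and tested at two-sided 0.05.

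**The concern.** A patient can restart only after stopping. Short-arm patients stop at 48 h and controls at day 5, so for three days only one arm can produce the event. Two patients with the same infection, proven on the same day and both treated, are then scored differently because of their allocation. Adjustment for age, sex, approach, type of appendicitis, ASA score and center cannot remove this, because the difference is created by the arm itself.

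Restart is one of the few secondary outcomes named in the abstract. Readers will take a higher restart rate as a sign that 48 h was too short. Part of such a difference could be pure labelling, always in the direction unfavourable to the short course.

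Two neighbouring endpoints raise lesser points. A readmission requires a prior discharge, and the short arm can go home sooner. Time to discharge criteria may be unobserved for a patient sent home before meeting them.

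**Working it through.** **The plan's own figure.** The article gives no number for these endpoints, so the check borrows its arm size. With a 15% rate, a 7.5-point margin, one-sided 0.025 and 90% power:

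n per arm = (1.960 + 1.2816)² × 2 × 0.15 × 0.85 / 0.075² = 10.51 × 0.255 / 0.005625 ≈ 477, or 954 in total. The article states 960, and power at 480 per arm is 90.2%. Allowing for dropout, 960 / 0.90 = 1067 against 1066 stated. The sample size reproduces, and 480 per arm is used below.

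**Inputs.**
- Stopping times: 48 h and day 5 (Postoperative antibiotic treatment).
- p, the risk of an infection first proven after 48 h, set equal in both arms. Upper value 15%, the expected primary endpoint rate (Sample size calculation). Lower value 10%, near the summed wound infection and abscess rates of the Dutch cohort in the Discussion: 1.3 + 8.0 = 9.3% and 1.6 + 8.9 = 10.5%.
- f, the share of those infections proven between 48 h and day 5. **This is an assumption; the documents do not give it.** Range shown: 5% to 40%.
- Every such infection is treated with antibiotics. In controls, one proven before day 5 leads to prolongation or a switch, not to a stop and later restart.

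Infections proven before 48 h are prolongations in both arms and cancel.

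**Formula.** Restart proportion: short arm p; control arm p × (1 − f); difference p × f. The chance of p < 0.05 against the short course is Φ[(d − 1.96 × SE₀) / SE₁], where d is the difference, SE₀ the pooled and SE₁ the unpooled standard error, at 480 per arm.

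| p | f (assumed) | Short arm | Control arm | Difference (points) | Chance of p < 0.05 |
|---|---|---|---|---|---|
| 10% | 5% | 10.0% | 9.5% | 0.5 | 4.5% |
| 10% | 20% | 10.0% | 8.0% | 2.0 | 19% |
| 10% | 40% | 10.0% | 6.0% | 4.0 | 63% |
| 15% | 5% | 15.0% | 14.25% | 0.75 | 5.1% |
| 15% | 20% | 15.0% | 12.0% | 3.0 | 27% |
| 15% | 40% | 15.0% | 9.0% | 6.0 | 82% |

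If prolongation and switch for infection are counted as well, both arms score p and the difference is zero under the same assumptions.

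**Readmission.** The Discussion says that blinding would require short-arm patients to remain admitted, which implies that they otherwise leave sooner. The amount p × f is only an upper bound here. It is reached if every short-arm patient with such an infection is already home and every control is still admitted.

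**Time to discharge criteria.** Temperature, oral intake, mobility and pain on oral analgesia contain no antibiotic or IV item. Course length therefore does not enter the definition, and the arithmetic above does not apply. What remains is that the criteria do not bind discharge. If daily recording ends at discharge, a patient who leaves with a criterion unmet has no observed time, and linear regression has no means of using that record.

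**The case against.** The best defence is that the definition of restart is not in view. The article sends the decision algorithm and the variable list to the full protocol, and restart may be defined there to include prolongation. That stands as a caution: if so, the sponsor need only confirm it. It does not remove the point, because the article itself separates the two actions and names only one as the endpoint.

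Second, a reader is not left with restart alone. Antibiotic duration and the separate infection rates are also reported, and the infection rates do compare infection directly. That stands too, and limits the harm. It does not make the restart comparison interpretable.

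Third, the size rests on an unknown timing share. This is correct: at f = 5% the artefact is under one point and would hardly ever matter.

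A reader might also infer that readmission is biased in the same way. The documents do not support that. Having to come back is a real burden of going home sooner, just as a shorter stay is an advantage that the design rationale names. Length of stay is likewise an intended effect, not an artefact.

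A reader might further infer that time to discharge criteria runs on an arm-dependent clock. It does not, because none of its components refers to antibiotics. How often patients leave with criteria unmet, in either arm, is not given, so no size can be put on the ascertainment problem.

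**Conclusion.** The point holds for restart. As the article words it, the endpoint gives the arms different periods in which the event can occur, and under equal infection risk it differs by p × f against the short course. For p of 10–15% and f of 5–40% that is about 0.5 to 6 points. The direction follows from the design; the size depends on an assumed f and on all such infections being treated with antibiotics. Wound infections managed without antibiotics would shrink it.

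Readmission is a valid endpoint that needs a companion measure, because earlier discharge alone can turn an in-hospital event into a readmission. Time to discharge criteria has only the narrow problem of times unobserved at discharge.

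Nothing here touches the primary result. The composite is counted within 90 days of appendectomy in both arms, and the margin and sample size stand.

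**What to change.** - **Restart.** Define the endpoint as any therapeutic antibiotic treatment for infection beyond the allocated course, whether restart, prolongation or switch, from appendectomy to day 90 in both arms. Report total antibiotic days to day 90 beside it. The window should not begin at day 5, since that would hide a short-arm restart begun and ended on days 3–4. Tabulate separately any switch made for an adverse reaction, or on a culture result without a newly proven infection: these have five days in which to occur in one arm and two in the other. If the full protocol already defines restart this broadly, say so.
- **Readmission.** Keep the rate and report total hospital days to day 90, index stay plus readmissions, beside it.
- **Time to discharge criteria.** Use a time-to-event analysis from appendectomy in place of linear regression. Add a sensitivity analysis, because censoring at discharge may be informative: discharge is a clinical judgement linked to recovery. Report by arm how many patients left with criteria unmet.

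The cost is endpoint wording and analysis text. Antibiotic duration and regimen, hospital stay, readmissions and the daily criteria are already to be recorded. The sample size and the conduct of the trial do not change. With 165 of 1066 patients randomized when the article was completed, the definitions can be settled before any comparison of these endpoints.
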